# Effectiveness of a guided ACT-based self-help resilience training for depressive symptoms during pregnancy: Study protocol of a randomized controlled trial embedded in a prospective cohort

**DOI:** 10.1186/s12884-020-03395-9

**Published:** 2020-11-19

**Keywords:** Peripartum depression, Resilience, Psychological outcome, Infant development, Cortisol

## Abstract

**Background:**

During pregnancy, about 10 to 20% of women experience depressive symptoms. Subclinical depression increases the risk of peripartum depression, maternal neuro-endocrine dysregulations, and adverse birth and infant outcomes. Current treatments often comprise face-to-face psychological or pharmacological treatments that may be too intensive for women with subclinical depression leading to drop-out and moderate effectiveness. Therefore, easily accessible, resilience enhancing and less stigmatizing interventions are needed to prevent the development of clinical depression. This paper describes the protocol of a prospective cohort study with an embedded randomized controlled trial (RCT) that aims to improve mental resilience in a sample of pregnant women through a self-help program based on the principles of Acceptance and Commitment Therapy (ACT). Maternal and offspring correlates of the trajectories of peripartum depressive symptoms will also be studied.

**Methods:**

Pregnant women (≥ 18 years) receiving care in Dutch midwifery practices will participate in a prospective cohort study (n ~ 3500). Between 12 and 18 weeks of pregnancy, all women will be screened for depression with the Edinburgh Postnatal Depression Scale (EPDS). Women with an EPDS score ≥ 11 will be evaluated with a structured clinical interview. Participants with subclinical depression (*n* = 290) will be randomized to a 9-week guided self-help ACT-training or to care as usual (CAU). Primary outcomes (depressive symptoms and resilience) and secondary outcomes (e.g. anxiety and PTSD, bonding, infant development) will be collected via online questionnaires at four prospective assessments around 20 weeks and 30 weeks gestation and at 6 weeks and 4 months postpartum. Maternal hair cortisol concentrations will be assessed in a subsample of women with a range of depressive symptoms (*n* = 300). The intervention’s feasibility will be assessed through qualitative interviews in a subsample of participants (*n* = 20).

**Discussion:**

This is the first study to assess the effectiveness of an easy to administer intervention strategy to prevent adverse mental health effects through enhancing resilience in pregnant women with antepartum depressive symptomatology. This longitudinal study will provide insights into trajectories of peripartum depressive symptoms in relation to resilience, maternal cortisol, psychological outcomes, and infant developmental milestones.

**Trial registration:**

Netherlands Trial Register (NTR), NL7499. Registered 5 February 2019.

## Background

Antepartum depressive symptoms and subclinical depression with prevalence rates ranging from 10 to 20%, often remain unnoticed by maternity care providers during antenatal visits [1]. However, early detection is crucial because symptoms of depression or anxiety may result in antepartum depression with prevalence rates ranging from 5 to 13% or in postpartum depression (PPD) with prevalence rates of 10 to 15% [2, 3]. Because these depressive disorders are associated with reduced family functioning, impaired mother-to-infant bonding, adverse birth outcomes such as preterm birth, and cognitive and behavioral developmental delays in the infant, they form an essential treatment target [4–10]. A potential mechanism underlying these associations is stress-induced neuroendocrine dysregulation of the maternal Hypothalamic Pituitary Adrenal (HPA)-axis reflected by increased maternal cortisol levels that, in turn, affects the functioning of the neonatal HPA-axis [11].

An important protective factor against the development of depression is resilience: adapting to and recovering from stress [12]. Promoting resilience and positive mental health is a priority of the World Health Organization (WHO) [13]. However, little is known about resilience in the antepartum period and its preventive effect on maternal depressive symptoms and infant neurodevelopmental outcomes. In non-pregnant populations, positive associations between resilience and psychological well-being have been observed [12]. To date, only a few small studies have examined associations between levels of resilience (or related factors) and maternal depression and depressive symptoms or infant behavioral and developmental outcomes [14–16]. More specifically, by examining trajectories of antepartum and postpartum depressive symptoms in association with maternal antepartum resilience, psychological well-being, and developmental outcomes of the young child, a better understanding of individualized treatment options can be gained. Recently, researchers of a prospective cohort study (*n* = 2466) identified antepartum and postpartum risk factors (e.g., younger age, smoking, nausea, operative delivery, bonding difficulties, and low partner support) of several maternal depressive trajectories [17]. However, to date, additional examination of other psychological characteristics, including resilience and (chronic) neurobiological correlates associated with these trajectories, is lacking. New studies may provide evidence for relevant clinical management and treatment options for the near future.

Several international guidelines underscore the necessity to screen more adequately for antepartum depression or (subclinical) symptomatology. Guidelines also advise maternal healthcare providers to be aware that women may be unwilling to disclose their mental health issues and may be reluctant to engage in treatment due to fear of stigmatization [18, 19]. After detection of subclinical depressive symptoms, there is a clear need for effective interventions. Despite the advice for high-intensity psychological interventions such as cognitive-behavioral therapy (CBT) and interpersonal therapy [18], these interventions are less effective in women with subclinical antepartum or postpartum depression or show no effect at all in non-help-seeking women [20, 21]. An important problem of previous RCTs with high-intensity interventions to prevent perinatal depression are high attrition rates (e.g. on average 20%), likely because pregnant women are faced with practical demands (e.g., time constraints, lack of childcare), the stigma of experiencing psychological problems during pregnancy and physical issues [20]. From previous trials, we also know that to overcome high attrition rates and improve effectiveness, interventions should be aimed primarily at at-risk women (e.g., women with subclinical depression) and should fit the unique preferences and needs of pregnant women [22–24].

Psychological interventions that aim to improve mental resilience through self-help training might offer a less stigmatizing and more fruitful approach during pregnancy [25]. In general populations, a low level of antepartum resilience is associated with an increased risk of ante- and postpartum depression [26], while improving resilience has shown to prevent the development and recurrence of depression and other adverse outcomes such as PTSD [12, 27]. Interventions that aim to enhance resilience by improving stress-recovery in response to daily stressors, positivity, and flexibility such as Acceptance and Commitment Therapy (ACT) have already proven to be effective for non-pregnant individuals with subclinical depression [28]. Meta-analyses have shown that ACT, an innovative form of CBT, has a larger potential to induce psychological benefits and effectiveness in the long-term than classical CBT approaches [29, 30]. Although a four-session ACT-based group intervention in pregnancy has recently been developed [31], ACT’s effectiveness has not yet been evaluated among pregnant women with subclinical depression.

Exposure to (traumatic) stress before or during pregnancy is a significant risk factor for developing peripartum depression and anxiety and may result in less favorable outcomes for child development, family functioning, and physiological stress dysregulation [32–34]. During the early course of this (ongoing) research project, the COVID-19 pandemic unfolded and may have provoked additional prenatal stressors such as fear of getting infected, potential adverse health effects for the (unborn) baby, financial setbacks, and social distancing measures that may also affect maternity care. Research into natural disasters has shown that children in utero exposed to maternal prenatal stress display more adverse birth outcomes and infant developmental- and health outcomes [35, 36]. However, little is known about the potential buffering effect of maternal resilience on adverse effects of prenatal stress (due to e.g. COVID-19) on maternal mental health and infant development.

In this ongoing prospective cohort study, antepartum depression levels are measured in Dutch pregnant women (*n* = 3500). Subsequently, women with subclinical depression levels will be randomized to a guided self-help ACT-based resilience program or to care as usual (CAU). The short- and long-term effectiveness and feasibility of the intervention will be assessed using quantitative RCT data at multiple time-points and qualitative interviews. The prospective cohort data will be used to examine trajectories of different levels of peripartum depression and identify maternal psychosocial factors (i.e. stress and resilience) and demographic, neuroendocrine, and child-developmental factors that may characterize these trajectories.

## Method

### Study design

This study is designed as a prospective cohort study with an embedded randomized controlled trial (RCT) (Fig. 1). All women participating in the cohort study will be screened for depression at 12–18 weeks gestation. Women with subclinical depression will then be randomly allocated to either a guided self-help resilience program of 9 weeks (intervention) or care as usual (CAU) provided by maternity healthcare providers. All participants will be assessed at approximately 14–20 weeks (T1, RCT pre-intervention), at 28–32 weeks (T2, RCT one week post-intervention) gestation and postpartum at 6 weeks (T3) and 4 months (T4). Birth outcomes at T3 will be derived through data-linkage with the Dutch national perinatal registry [37]. Two additional sub-studies will be conducted to assess: (1) maternal cortisol levels (hair cortisol concentration (HCC)) in 300 participants randomly selected from the cohort study following T0, and (2) feasibility of the intervention via interviews with approximately 20 participants in the intervention group following T2. The Ethics Review Board of the VU University Medical Center has approved the study protocol (certificate number NL64740.029.18).

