### Participants, eligibility, and screening

Women are eligible to participate when aged ≥ 18 years, receiving antepartum care at the moment of inclusion. Women will be excluded when they do not master the Dutch language sufficiently. After informed consent, all women will participate in a screening procedure for depressive symptoms (T0; 12–18 weeks gestation) and subsequent online assessments throughout pregnancy and postpartum (Fig. 1; T1 – T4).

For the embedded RCT, an additional inclusion criterion is an EPDS score of ≥ 11 [38] with or without a mild depressive disorder (i.e. a subclinical depression) as based on a structured clinical interview by telephone assessing the presence and severity of current depressive or dysthymic disorders and suicidality with the Mini International Neuropsychiatric Interview (MINI) supplemented with the Sheehan Disability Scale (SDS) [39–41]. The RCT’s exclusion criteria are psychopharmacological and/or psychological treatment over the past three months (reported by the participant), a current major depressive disorder, and/or moderate to high suicide risk (based on the MINI).

Additional inclusion criteria for the HCC sub-study are willing to provide a hair sample and sufficient hair growth at the posterior vertex of the head with a length of at least 1 cm. Women who used oral corticosteroids in the previous 3 months will be excluded from participation in the HCC sub-study.

For the qualitative sub-study, participants in the RCT will be purposively sampled from the intervention group to assess the self-help resilience training experiences. We will include a sample of ca. 20 women. The sample consists of women with improved EPDS scores (< 11) and women with continued depressive symptoms at T2 (EPDS score ≥ 11) as well as women who did or did not complete the full training and modules of the intervention.

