After the screening procedure (T0), all study-participants will receive URL-links to the digital baseline- (T1) and follow-up questionnaires (T2-T4; Fig. 1). Each digital questionnaire assessment (T1-T4) will take approximately 30 minutes to complete. Researchers can analyze data collected through this web-based data-gathering tool without having access to information about the allocation.

For the HCC sub-study, a subsample of women will be asked to donate a hair sample at T1 (100 women with EPDS score < 11; 150 women with subclinical depression; 50 women with major depressive or dysthymic disorder based on the MINI). Hair samples will be collected at 14 to 20 weeks’ gestation. Due to COVID-19, partners (or other family members) will be asked to collect the participants’ hair samples at home. An instruction video will be shared for this purpose. Participants and their partners will be instructed to watch this video before hair sample collection to ensure a standardized hair sampling method. Hair strands of approximately 100 to 150 hairs will be cut as close as possible from the scalp from a posterior vertex position [42]. The most proximal 3 cm of hair will be used for laboratory analysis. Based on a mean hair growth rate of 1 cm per month, the hair samples reflect the cumulative cortisol and cortisone secretion of the previous 3 months. Participants of the HCC sub-study will be asked to provide additional written informed consent.

For the qualitative sub-study, a sub-sample of women from the intervention arm will be recruited via ‘purposively sampling’ approximately two weeks after the post-intervention assessment (T2). They will participate in a qualitative interview of 30–40 minutes (provided they have given additional consent). Interviews will be conducted using a topic-list with open-ended questions addressing the following substantive points during the interviews: (emotional) experience of the resilience-course, experiences of the e-mail coaching, working mechanisms, and point(s) of improvement of the intervention. Counselors will also be interviewed concerning the course of the intervention. A trained interviewer will conduct interviews. Results will provide important information for (process)evaluation, optimization, and future implementation of pregnant subclinically depressed women’s resilience course.

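### The hair-cortisol sub-study is called a random sample of the cohort but is fixed by symptom quotas, and it admits 1 cm hair although 3 cm is assayed

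*Protocol article*

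**What the plan says.** **Selection.** The protocol article describes the sub-study in three places. Study design says cortisol is assessed "in 300 participants randomly selected from the cohort study following T0". Study procedure says hair is requested at T1 from "100 women with EPDS score < 11; 150 women with subclinical depression; 50 women with major depressive or dysthymic disorder based on the MINI". The abstract says only that it is measured "in a subsample of women with a range of depressive symptoms". None of the three says that selection is random within symptom groups.

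**Hair length.** The eligibility section requires "sufficient hair growth at the posterior vertex of the head with a length of at least 1 cm". Study procedure then states: "The most proximal 3 cm of hair will be used for laboratory analysis". It assumes growth of 1 cm per month and concludes that "the hair samples reflect the cumulative cortisol and cortisone secretion of the previous 3 months". On timing it says: "Hair samples will be collected at 14 to 20 weeks’ gestation". No rule is given for hair between 1 and 3 cm.

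**Use of the data.** Statistical analyses treats cortisol as a correlate of depressive-symptom trajectories, using (generalized) linear mixed models. The adjustment variables named as examples are parity, educational level and ethnicity.

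**The concern.** A random sample of the cohort and a sample filled to 100/150/50 by EPDS and MINI status are different designs. Someone relying on Study design would take the 300 as representative and could report a mean cortisol or a distribution from them as a cohort figure. Under the quotas, two thirds of the 300 were chosen because of their symptom level, which is closely tied to the trajectories that cortisol is meant to help characterise. The text should say so, and the cortisol models should reflect it.

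The hair criterion raises a separate problem. A woman with 1 to under 3 cm of hair is eligible but cannot supply the segment to be assayed. If she is kept, her value covers a shorter and later part of pregnancy than the three months stated for everyone.

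**Working it through.** **Inputs**
- Cohort of about 3500, of whom about 15% have depressive symptoms (Power calculation). The Background gives 10 to 20%, used here as a range. The 15% is taken as the share with EPDS ≥ 11.
- Quotas of 100, 150 and 50 (Study procedure).
- Refusal 20% and exclusion 25% among potential trial participants (Power calculation).
- Growth of 1 cm per month, sampling at 14 to 20 weeks (Study procedure).

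**Step 1: the plan's own figures.** The quotas give 100 + 150 + 50 = 300, as stated. Screen-positive women: 3500 × 0.15 = 525. Expected in the trial: 525 × (1 − 0.20 − 0.25) = 289, matching the stated 290 or so. The 150 subclinical women would be 150/290 = 52% of the trial. The number with major depressive or dysthymic disorder is not given. Exclusions for all reasons come to 525 × 0.25 = 131, so 50 is not ruled out.

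**Step 2: what a simple random draw would give.** The expected number with EPDS ≥ 11 is 300 × prevalence. The ranges are hypergeometric (300 drawn from 3500).

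| Prevalence | Expected EPDS ≥ 11 | 95% range | Expected EPDS < 11 |
|---|---|---|---|
| 10% | 30 | 21 to 40 | 270 |
| 15% | 45 | 34 to 57 | 255 |
| 20% | 60 | 47 to 73 | 240 |

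The quotas require 150 + 50 = 200 and 100. The chance of drawing 200 or more with EPDS ≥ 11 is effectively zero in every row.

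**Step 3: degree of enrichment at 15%.**
- EPDS ≥ 11: 200/525 = 38.1% sampled.
- EPDS < 11: 100/(3500 − 525) = 100/2975 = 3.4% sampled.
- Ratio: 0.381/0.0336 = 11.3. In general it is 2 × (1 − p)/p, which gives 18 at 10% prevalence and 8 at 20%.
- Share with EPDS ≥ 11: 200/300 = 67% in the sub-study against 15% in the cohort.

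**Step 4: cost of weighting back to the cohort.** The inverse-fraction weights are 2975/100 = 29.75 and 525/200 = 2.625. The Kish effective sample size is (Σw)²/Σw² = 3500² / (100 × 29.75² + 200 × 2.625²) = 12,250,000 / 89,884 = 136. This uses two strata, because the documents do not split the 525 between subclinical and disorder.

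**Step 5: exposure window.** The months covered equal the length in cm. Taking 4.345 weeks per month, the window opens at the sampling week minus 4.345 × length.

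| Length | Months covered | Window opens (sampled at week 14 / week 20) |
|---|---|---|
| 1 cm | 1 | week 9.7 / 15.7 |
| 2 cm | 2 | week 5.3 / 11.3 |
| 3 cm | 3 | week 1.0 / 7.0 |

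Only hair of 3 cm or more gives the stated three months. The corticosteroid exclusion in the eligibility section also looks back 3 months, so the 1 cm minimum is the figure out of line with the rest.

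**The case against.** The three descriptions can be read together. Selection takes place after T0, when EPDS status is known, and the abstract speaks of a range of symptoms, so random selection within symptom groups is a natural reading. Enriching for symptomatic women is an ordinary choice, and weighting is a detail that an article may leave to the analysis plan. All of this stands. What remains is that Study design, as worded, names a different scheme.

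Two stronger readings are tempting. A reader might infer that the group sizes are not those stated. The documents do not support this: the only sizes given are the quotas, they add to 300, and Step 1 shows nothing that puts them out of reach. A reader might also infer that comparisons between depression groups would be underpowered. That would need a simple random draw, which the quotas rule out, and a disorder-versus-low-symptom contrast, which no section plans. No power claim is made for the sub-study.

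The harm should not be overstated either. No section announces a cohort mean cortisol from the 300, and the trajectory classes are not said to be restricted to them. In a simulation with assumed cohort shares of 85/10/5% for the three groups, linear cortisol slopes moved by 5% or less. Those shares are not from the documents, so this is only indicative, but it suggests that the planned association is less exposed than a cohort-level summary.

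On hair, no section says that short samples will be analysed as three months. Their handling is simply not stated, and the three-month reading is sound for hair of 3 cm or more.

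**Conclusion.** Both inconsistencies are in the current text and should be reconciled. The 300 are not a simple random sample of the cohort: 67% have EPDS ≥ 11 against about 15%, an enrichment of about 11-fold by sampling fraction (8- to 18-fold over 20% to 10% prevalence). These figures rest on the planned cohort of 3500 and would shift with actual enrolment and consent to hair sampling. The fault lies in the description of selection, not in the quotas.

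The 1 cm minimum does not fit the 3 cm segment or the three-month statement. Hair of 1 to under 3 cm covers 1 to under 3 months. How many women this concerns cannot be worked out from the document.

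The issue is confined to a secondary sub-study. The randomised trial's primary outcomes and its planned 290 women are untouched.

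**What to change.** **Selection.** In Study design, replace the statement of random selection from the cohort with selection within three strata defined by T0 EPDS and MINI status (100/150/50), and say whether selection within each stratum is random. Record how many cohort women fall in each stratum. Include stratum in the cortisol models; the cortisol coefficient is then read conditional on screening status. Use inverse-sampling-fraction weights only for an estimate meant to describe the whole cohort. The cost is a wording change and one recorded variable, but weighted estimates are appreciably less precise, with an effective n of about 136 instead of 300.

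**Hair length.** Align the eligibility section with Study procedure in one of two ways: require the length of the analysed segment (3 cm), or analyse one common shorter segment for everyone and change the three-month statement to match. The first excludes some short-haired women and changes an eligibility rule after enrolment has begun (757 women at publication), so samples already taken from shorter hair would need a stated rule. The second keeps those women but shortens the exposure window for all.

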**Fig. 1 Fig1:**
[figure not shown]
Flow-chart of the study

### Participants, eligibility, and screening

Women are eligible to participate when aged ≥ 18 years, receiving antepartum care at the moment of inclusion. Women will be excluded when they do not master the Dutch language sufficiently. After informed consent, all women will participate in a screening procedure for depressive symptoms (T0; 12–18 weeks gestation) and subsequent online assessments throughout pregnancy and postpartum (Fig. 1; T1 – T4).

For the embedded RCT, an additional inclusion criterion is an EPDS score of ≥ 11 [38] with or without a mild depressive disorder (i.e. a subclinical depression) as based on a structured clinical interview by telephone assessing the presence and severity of current depressive or dysthymic disorders and suicidality with the Mini International Neuropsychiatric Interview (MINI) supplemented with the Sheehan Disability Scale (SDS) [39–41]. The RCT’s exclusion criteria are psychopharmacological and/or psychological treatment over the past three months (reported by the participant), a current major depressive disorder, and/or moderate to high suicide risk (based on the MINI).

Additional inclusion criteria for the HCC sub-study are willing to provide a hair sample and sufficient hair growth at the posterior vertex of the head with a length of at least 1 cm. Women who used oral corticosteroids in the previous 3 months will be excluded from participation in the HCC sub-study.

For the qualitative sub-study, participants in the RCT will be purposively sampled from the intervention group to assess the self-help resilience training experiences. We will include a sample of ca. 20 women. The sample consists of women with improved EPDS scores (< 11) and women with continued depressive symptoms at T2 (EPDS score ≥ 11) as well as women who did or did not complete the full training and modules of the intervention.

